We have previously shown that HR can be used as a person-specific measure of reactivity for non-verbal patients [47]. To evaluate HR as a tool to assist pain management for non-verbal patients, other well-established biomarkers of pain, such as heart rate variability (HRV) and cytokine biomarkers in blood, should be utilized. HRV is a non-invasive measure of imbalances in the autonomic nervous system with a higher variance indicating less stress [48, 49]. A growing body of psychological research has shown HRV to be a stable biomarker of prolonged pain [50], and research supports an association between HRV and emotional responses [51, 52]. Recent studies suggest that certain circulating inflammatory cytokines can be utilized as reliable biomarkers for detecting chronic pain in various diseases [53–55]. Blood biomarkers of pain include MCP-1, IL-1RA, IL-8, TGFβ1, and IL-17 [53–55]. Elevated levels of these cytokine biomarkers have been associated with experimental pain and self-rated pain, and their levels have been shown to closely follow the temporal phenomenology of pain episodes [54]. The combination of HR, HRV and cytokine biomarkers may prove a novel tool for pain assessment.

Despite the potential of this approach, the use of sensors in care for non-verbal patients is not yet widespread. Most studies on sensors for pain management and communication has been conducted among patients with an ability to communicate [48, 56–60]. Non-verbal patients are frequently left out of research studies, even though advancements in medical technology could bring significant benefits to this patient population.

The proposed study is a randomized controlled trial that seeks to reduce incidence of pain for non-verbal individuals with autism and ID through use of HR-sensors. This study aims to 1) assess the effectiveness of HR as a tool to identify potentially painful care procedures; 2) test the impact of HR-informed changes on pain biomarkers; and 3) examine the impact of six weeks of HR monitoring on the quality of communication between patients and caregivers.

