#### Secondary objectives

The secondary objectives are to:

Evaluate how HR-informed changes in potentially painful procedures affect pain biomarkers.

*Secondary hypothesis 1: HR-informed changes in patient-specific care procedures (a. physiotherapy, b. applying cast for spastic limbs, c. transportation/being lifted, or d. routines for personal hygiene) will increase HRV and reduce pain-related cytokines (MCP-1, IL-1RA, IL-8, TGFβ1, and IL-17) as evaluated at the beginning, mid-way and at the end of the study period.*

2)Assess how six weeks of communication through HR affects the quality of communication between patient and caregiver.

*Secondary hypothesis 2: HR as an aid in communication will increase caregivers’ understanding of the patient as measured by changes in perceived understanding of the patient from the beginning to the end of the study period.*

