#### HRV monitoring of prolonged pain

HRV is a non-invasive measure of parasympathetic nervous system activity [74, 75]. Lower levels of HRV (i.e., reduced parasympathetic nervous system activity) have been associated with both poor somatic and psychiatric health [76, 77]. Like the HR, HRV is calculated continuously through the Polar OH1 armband. Additionally, HRV will be assessed at rest with a portable electrocardiogram (ECG). The ECG will be collected at baseline, after two weeks of intervention in the early group, and at the end of the study period.

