#### Analysis of secondary objectives

To test evaluate the effect of using HR in improving care procedures and reducing pain, one-tailed paired samples t-tests are used to test for difference in HRV and cytokine biomarkers (MCP-1, IL-1RA, IL-8, TGFβ1, and IL-17) before and after intervention (secondary hypothesis 1). Cohen’s *d* values [94] will also be calculated to determine the size of the effect. To evaluate the effect of HR-informed changes in procedures, differences in biomarker scores across the early and delayed groups will be analysed using Wilcoxon Signed-rank test, which can evaluate whether the difference scores from each group are not equal (i.e., that they are significantly different). Critical P-values for the five cytokine measurers will be corrected for multiple comparisons using a 5% false discovery rate [95].

To test for significant change in rates of understanding the patient throughout study period (secondary hypothesis 2), we will perform one-tailed paired sampled t-tests. Additionally, Spearman’s rank-order correlation (*r*_s_) is used to investigate relationships between HR measures and caregivers report on NCPC and caregivers report on perceived understanding of the patient.

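### The 5% false discovery rate omits HRV, and the protocol does not say whether it spans both comparisons or which comparison decides secondary hypothesis 1

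*Protocol article*

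**What the plan says.** Under Secondary objectives, the hypothesis is that changed care procedures "will increase HRV and reduce pain-related cytokines", so HRV and the cytokines belong to one hypothesis. The Background also counts HRV among the biomarkers: "other well-established biomarkers of pain, such as heart rate variability (HRV) and cytokine biomarkers in blood".

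Analysis of secondary objectives then gives three statements in this order:

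1. For before versus after, "one-tailed paired samples t-tests are used to test for difference in HRV and cytokine biomarkers". This sentence carries the label of secondary hypothesis 1.
2. For the randomised groups, "differences in biomarker scores across the early and delayed groups will be analysed using Wilcoxon Signed-rank test". Its stated purpose is to evaluate the effect of the HR-informed procedure changes, which is the subject of the same hypothesis.
3. For multiplicity, "Critical P-values for the five cytokine measurers will be corrected for multiple comparisons using a 5% false discovery rate".

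Nothing further says which comparison decides the hypothesis or how many biomarkers must be significant to support it. Only the later work on alarm thresholds is labelled exploratory.

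**The concern.** The article states a multiplicity rule, but its boundary does not match the hypothesis. Six biomarkers answer secondary hypothesis 1 and the rule covers five. HRV is judged at a full 5% beside the corrected family. The rule is also silent on whether the cytokine tests from the two comparisons form one family or two.

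The two comparisons do not carry equal weight. According to Study design overview and the section on assigning participants, the delayed group exists to separate formal procedure changes from the attention that comes with taking part. Before/after tests cannot make that separation. As written, a chance before/after HRV result at an uncorrected 5% could be reported as support for the hypothesis even if the randomised comparison showed nothing.

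**Working it through.** **Inputs.**
- Six biomarkers and two comparisons, with a 5% false discovery rate on the five cytokines (Analysis of secondary objectives).
- HRV counted as a biomarker in both comparisons (Background).
- Alpha 0.05 for each uncorrected test. The protocol gives this only under Sample size, so applying it here is an assumption.
- 38 patients, 19 per group.
- Benjamini-Hochberg as the procedure. The text cites a method without naming it, so this is an assumption.
- Correlation between biomarkers is not given, so a range is used.

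**The plan's own figure.** When nothing changes, Benjamini-Hochberg over five independent tests gives a 5% chance of any rejection. Simulation gives 5.0%, so the stated 5% is reproduced for the cytokines alone.

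**Independent tests.** Each corrected family and each uncorrected HRV test is one unit at 0.05, and the chance of at least one false result over k units is 1 − 0.95^k.
- Before/after only, cytokine family plus HRV: 1 − 0.95² = 9.8%.
- Both comparisons, one family over ten cytokine tests plus HRV twice: 1 − 0.95³ = 14.3%.
- Both comparisons, a cytokine family in each plus HRV in each: 1 − 0.95⁴ = 18.5%.

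**Correlated tests.** 20,000 simulated null trials were run, with one-sided paired t-tests before/after and a two-sided rank-sum test between groups. The rank-sum test stands in because the signed-rank test does not fit two independent groups. The table shows the chance of at least one significant result, unless stated otherwise.

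| Reading | corr. 0 | 0.3 | 0.5 | 0.7 | 0.9 |
|---|---|---|---|---|---|
| Five cytokines alone, before/after | 5.0% | 4.6% | 4.5% | 4.3% | 3.4% |
| Before/after: cytokine family + HRV | 9.8% | 9.1% | 8.0% | 7.2% | 5.6% |
| Both: one family of ten + HRV twice | 13.5% | 13.2% | 12.5% | 11.5% | 10.0% |
| Both: a family in each + HRV in each | 18.0% | 16.8% | 15.5% | 13.7% | 11.1% |
| HRV and at least one cytokine required, before/after | 0.2% | 0.8% | 1.4% | 2.2% | 2.8% |
| All six in one family, one comparison | 5.1% | 4.6% | 4.5% | 4.1% | 3.2% |

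A separate simulation of 300,000 null trials, with all test statistics equally correlated from 0 to 0.8, gives 9.8% down to 6.2% for before/after. For both sets with a family in each it gives 18.6% down to 10.2%.

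**Sensitivities.**
- If HRV were not tested between groups, the figure for both sets would be 13.8% at correlation 0 and 8.5% at 0.9.
- The between-group test is described as non-directional, so results in either direction are counted. Counting only the favourable direction makes each between-group unit about 0.025. At independence that gives 1 − 0.95² × 0.975² = 14.2%.
- There are two HRV sources, the armband and a resting recording ("Additionally, HRV will be assessed at rest with a portable electrocardiogram (ECG"). The figures count only one.

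**Detectable effect at 80% power, one-sided 5%.** The noncentrality is d√n for a paired test on n patients and d√(n/2) for two groups of n. Paired with n = 38 gives d = 0.41, and two groups of 19 give d = 0.82. The protocol's Fig. 3 legend states 0.82 but attributes it to a paired test on 38.

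**The case against.** The strongest reply is that the hypothesis is worded as a conjunction: HRV rises and cytokines fall. If HRV and at least one cytokine were both needed, the false-claim chance would be 0.2% to 2.8% and there would be nothing to correct. That arithmetic stands. But the protocol states no such rule and tests each biomarker separately, so a single significant result could be reported as support.

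Second, HRV is a different kind of measure from a blood panel, and correcting within the panel alone is a defensible convention for secondary outcomes. This is a condensed article, and an ordering of secondary tests may stand in an analysis plan that is not shown. The lack of a hierarchy would therefore not be a finding by itself. The point rests on the rule the article does state, which leaves out one biomarker of its own hypothesis and is unclear about its span.

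Three stronger readings are tempting and are not supported:

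- A reader might infer that the whole early-versus-delayed set is uncorrected, which would give 16.6% to 33.2% in simulation. The correction sentence directly follows the early-versus-delayed sentence and is not limited to the before/after tests. The cytokine tests of that comparison may well be covered.
- A reader might infer that a promised 5% error rate for the hypothesis is broken. The protocol promises a 5% false discovery rate for five cytokines and no family-wise rate for secondary hypothesis 1.
- A reader might settle on one figure near 15%. That needs a correlation of about 0.5, which the protocol does not give, so only a range can be defended.

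**Conclusion.** The point holds in a limited form. The false discovery rate omits HRV, does not say whether it spans both comparisons, and leaves open which comparison decides secondary hypothesis 1. If any one significant biomarker counts, the chance of a false claim when nothing changes is about 6% to 10% for the before/after set and about 10% to 18% for both sets with the cytokines corrected. These figures assume 0.05 for each uncorrected test, Benjamini-Hochberg for the cytokines, HRV tested in both comparisons, between-group results counted in either direction, and correlations from 0 to 0.8. Under a rule requiring both HRV and a cytokine the inflation disappears, so the size depends on a choice the protocol leaves open. The primary hypothesis is not affected.

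**What to change.** In Analysis of secondary objectives:

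1. Name the randomised early-versus-delayed comparison of change from baseline to the mid-way measurement as the test that decides secondary hypothesis 1. Table 1 places that measurement in week 4 and the Fig. 2 legend at the end of week 3. Both precede the delayed group's start in week 5, but the two should be reconciled.
2. Use a test for two independent groups, such as the rank-sum test, in place of the signed-rank test.
3. Apply one 5% false discovery rate to all six biomarkers in that comparison, and say which HRV measure is the sixth. This brings the chance of any false result to about 5% or less (5.1% simulated at correlation 0, 3.2% at 0.9).
4. Report the before/after results as supportive estimates with confidence intervals and without significance claims.

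This takes a few sentences and no new data, but it has two costs:

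- **HRV is judged more strictly.** Under Benjamini-Hochberg its threshold runs from 0.05/6 = 0.0083, if it is the only biomarker to move, up to 0.05 if all six do.
- **Power falls relative to the paired tests.** The deciding comparison detects about d = 0.82 with 19 per group, against about 0.41 for a paired test on 38. The 0.82 is for a one-sided 5% test. Two-sided it is 0.93. With the planned 15% dropout (38 × 0.85 = 32.3, about 16 per group) it is 0.90 one-sided and 1.02 two-sided. The false discovery correction raises these further.

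Since 0.82 is the detectable effect the protocol already states in the Fig. 3 legend, the change stays close to the stated design sensitivity, but the power cost should be disclosed.

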#### Exploratory post-hoc analysis

With the goal of further developing the technology of the HR-alarm and software, we will do exploratory analysis on how settings of alarm thresholds in the post-processing scripts compare with the event logs.

#### Administrative, ethical, regulatory considerations

The study will be conducted according to the Declaration of Helsinki.

Minor pain might occur as part of the project; this includes from possible skin reactions to the HR monitor, and pain associated with blood sample collection. For some, the HR monitor can be provocative emotionally, and some might be sensitive to new objects. Ideally, the use of the HR monitor should protect the participant from discomfort.

To maintain confidentiality, all laboratory specimens, evaluation forms, reports and other records will be identified by a coded number and initials only. All study records will be kept in a locked file cabinet and code sheets linking a patient’s name to a patient identification number will be stored separately in another locked file cabinet. Clinical information will not be released without the written permission of the participant. The investigators must also comply with all applicable privacy regulations (e.g., the Health Insurance Portability and Accountability Act of 1996, EU Data Protection Directive 95/46/EC).

#### Informed consent form

Informed consent will be obtained in accordance with the Declaration of Helsinki. A properly executed, written, informed consent will be obtained from each caregiver to enter the participant into the trial. Information should be given in both oral and written form and legal representatives must be given ample opportunity to inquire about details of the study.

#### Criteria for discontinuing or modifying allocated interventions

The participants in this study are particularly vulnerable, in that they cannot unequivocally convey how they react to a study measure, such as an HR monitor or bloodwork. It is therefore important to have a high degree of transparency. We believe that we achieve this by involving patient representatives in our project group, and all administrative levels (district director, mayor, agency manager, head of the care homes) in addition to parents, guardians, and caregivers being informed. Several of the mentioned collaborators will, to varying degrees, be involved in the study itself, and the transparency that this entail means security for the participants.

An HR monitor, whether it is attached to the wrist, ankle, or around the chest, can cause skin reactions, both allergic and mechanical. In that case, it must be removed, and an alternative location must be considered, or the use of the HR monitor must be discontinued. Some people with ID and ASD can be very sensitive to new objects. If this applies to the HR monitor, an alternative location must be considered, or the use of the heart rate monitor must be terminated.

As a suitable situation to intervene on is defined by an occurrence of at least 10 for the two-week pre-intervention period, for some participants it might be the case that no suitable situation is identified. In such case, there will be no intervention. However, the patients will be included in the final data presentation, as they shed light on in what proportion of patients HR may be useful for guiding formal change in care.

For caregivers (parents, guardians, family members, and healthcare personnel) the use of HR monitors can potentially distract from other tasks or make the time spent with the non-verbal person feel unnecessarily technical. Alternative placement or termination of the study for the patient in question must be considered against the benefits of using the HR monitor. In cases where it is doubted if caregivers due to such stress do not reliably follow the study protocol, data will be excluded.

A participant may be discontinued from study treatment at any time if the participants’ representatives, the investigators, or the caregivers feel that it is not in the participant’s best interest to continue. Parents or guardians will be able to withdraw the patient from the study without any form of justification.

If a participant is withdrawn from treatment due to an adverse event, the participant will be followed and treated by the principal investigator until the abnormal parameter or symptom has resolved or stabilized.

All participants who discontinue study treatment should come with their parents/guardians for an early discontinuation visit as soon as possible and then should be encouraged to complete all remaining scheduled visits and procedures. Reasonable attempts will be made by the investigators to provide a reason for participant withdrawals. The number and overarching reason for discontinuation or removal of data will be reported in publication of results.

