### Study design

#### Intervention

The intervention comprises individualized routines to reduce pain in potential pain-inducing settings.

In the pre-intervention phase, HR is continuously collected for 8 h/day across potentially painful care situations. The primary caregiver will report on situations with an HR increase (Figs. 4 and 5).

As the caregiver is not blinded to the HR increases during the registration phase, we expect instantaneous changes made when the HR band communicated obvious acute pain (e.g. skin pinched while putting on cast). These instantaneous, non-formalized changes made by each caregiver is not regarded as “change in routine” but are registered as HR-informed adaptations. The intervention consists of a formal change in routine, and involved changes is written routine and training of staff for the chosen situation. Allocation into an early group and a delayed group helps distinguish the non-formal adaptations based on HR from the effect of formal changes in procedures of care.

Based on the two-week pre-intervention phase, one of four types of care procedures are chosen as the intervention target: 1) physiotherapy, 2) applying cast on spastic limb, 3) transportation/being lifted and 4) personal hygiene procedures. If there are several situations identified as candidates for intervention, selection will be based on a) level of reproducibility and b) magnitude of HR increase. The procedure must be easily recognizable. The situation should at have an HR-spike occurrence for at least 10 episodes during the recording period (i.e. on average 1 occurrence/day), with at least 80% of the situation resulting in HR-increase (reproducibility).

The intervention will be in one of four forms:changes in physiotherapy, e.g., less rigorous movement in the identified painful stretch,preparations for putting on corrective cast to stabilize joint and/or stretch spastic muscles,change in procedures for transportation/lifting, e.g., new technique or adjustments made to equipment, orrevised personal hygiene procedure.

If none of the predefined interventions fit the chosen stressor, a fitting intervention is constructed and will be described separately and in detail when the results of this study are published.

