#### Blinding

The identity of test and delayed intervention treatments will not be known when analysing data on the secondary outcome measure. Access to the randomization code will be strictly controlled.

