### Strategies to improve adherence to interventions

#### Measures of treatment compliance

Professional caregivers will be asked to what extent they, due to unplanned events, ended up missing registrations or deviating from the intervention protocol. Before every shift, the caregiver will have to sign a compliance to the intervention protocol, which also operates as a reminder for registrations. The leading caregiver will remind staff of the protocol at every shift meeting. Furthermore, all HR-increases are recorded automatically, and in addition the caregiver will be probed for contextual data for each HR-increase. The discrepancy between number of HR increases and number of contexts recorded gives us a measure of caregiver responsiveness.

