## Discussion

In this randomized blinded controlled trial, we aim to study HR to improve communication between patient and caregiver. This clinical study of HR-informed intervention represents an important contribution to the research and practice of developmental disabilities and communication difficulties. Studies on patients with limited communicative abilities are lacking (Table 4). Existing studies investigating severely limited communicative abilities are small and mainly descriptive. Larger studies on technologies for patients with communication disability exclude the most severely debilitated patients. Furthermore, considerable heterogeneity of participant level of communication disability makes for less clinically relevant findings. In the present study we strive to correct this.

**Table 4 Tab4:** Methodological advances of current trial relative to past sensor-technology intervention trials among patients with communication difficulties

Limitations in literature^a^	Current study features
Few controlled trials	Randomized controlled design
Small sample sized/insufficient power/case studies	A sample of 38 patients allowing us to detect an 0.80 effect size
Absence of studies using comparator interventions	Controlling for effect of study participation by including a group with delayed intervention
Exclusion of most vulnerable patients	Inclusion of profoundly disabled patients
Lack of standardized measures and biomarkers	HR, HRV and biochemical biomarkers in blood
No adherence data	Routine signing of protocol by secondary participants to measure adherence
Considerable heterogeneity of participants regarding type and level of communication need	Patients with ID ranging from severe to profound and ranging from ambulant to wheelchair user, loss of eyesight and hearing

^a^Based on published reviews [29, 96], and review of studies on PubMed and Google Scholar using the phrases “sensor-technology intervention intellectual disability” and “technology intervention communication difficulties”

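### A discretionary, unmasked rule excludes data after randomisation when caregiver adherence is in doubt because of monitor-related stress, and it can inflate the one-sided before-after tests

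*Protocol article*

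**What the plan says.** All references are to the protocol article.

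- **Exclusion rule** (Criteria for discontinuing or modifying allocated interventions): "In cases where it is doubted if caregivers due to such stress do not reliably follow the study protocol, data will be excluded". The stress meant is described just before: use of HR monitors may distract caregivers or make time with the patient feel too technical.
- **Reporting** (same section): "The number and overarching reason for discontinuation or removal of data will be reported in publication of results".
- **Adherence data** (Measures of treatment compliance): "The discrepancy between number of HR increases and number of contexts recorded gives us a measure of caregiver responsiveness". Caregivers also sign a compliance statement before each shift and are asked about missed registrations and deviations. The exclusion rule refers to none of this.
- **Masking** (Blinding): "The identity of test and delayed intervention treatments will not be known when analysing data on the secondary outcome measure". Delivery is open. The Intervention section says "As the caregiver is not blinded to the HR increases during the registration phase", and describes the intervention thus: "The intervention consists of a formal change in routine, and involved changes is written routine and training of staff for the chosen situation".
- **Tests** (Analysis of primary objectives; Analysis of secondary objectives): one-tailed paired tests for the primary comparison of situations within patients, for HRV and cytokines before and after intervention, and for caregiver understanding. The early and delayed groups are compared by a test of whether their difference scores are unequal.

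**The concern.** The sentence is mandatory in effect and subjective in its trigger. As stated, it lets someone who may know the allocation and have seen the HR data decide which data count.

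Such a rule is harmless only if the judgement is unrelated to outcome, and there are reasons to doubt that here. The burden of the monitor plausibly rises with the number of alarms, and alarms are the HR increases the trial counts. Caregivers who find the monitor burdensome may also be those who would report little gain in understanding the patient, which is secondary hypothesis 2. Both links are plausible inferences, not facts in the article.

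The unit of exclusion is open. If whole patients go, so do the blood cytokines and the HRV from resting ECG, which do not rely on what caregivers register.

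The rule also sits awkwardly beside the article's own reasoning. In the same section, patients with no suitable situation are kept because they show how often HR is useful. Homes where caregivers cannot work with the monitor are informative in the same way.

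**Working it through.** The plan gives no figure for the number of such exclusions or their relation to outcome, so there is nothing to reproduce. The check asks how far a few outcome-related exclusions move a test when there is no effect.

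**Inputs from the article:** 38 patients, 1:1 allocation (19 and 19), one-sided alpha 0.05 for the paired tests. The dropout allowance is 15%, and 0.15 × 38 = 5.7, so about 6 patients.

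**Assumptions (not in the article):** k = 2, 4 or 6 patients excluded. The correlation ρ between the adherence judgement and the outcome is 0.3 to 0.5, with 0 and 1 as limits. Those judged worst have the less favourable changes.

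**Model:** the change score X is standard normal with mean 0. The judgement is S = ρX + √(1 − ρ²)·Z, with Z independent standard normal. Drop the k patients with the lowest S, compute t = mean(X)·√(38 − k)/SD(X), and reject if t exceeds the 95% point of t with 37 − k degrees of freedom. There were 400,000 simulated trials per cell.

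| Excluded of 38 | ρ = 0 | ρ = 0.3 | ρ = 0.5 | Spurious mean change at ρ = 0.3 / 0.5 |
|---|---|---|---|---|
| 2 | 5.0% | 7.4% | 9.7% | 0.032 / 0.054 SD |
| 4 | 5.0% | 9.8% | 14.9% | 0.059 / 0.098 SD |
| 6 | 5.0% | 12.2% | 20.9% | 0.083 / 0.139 SD |

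**Hand check:** the rejection rate is roughly P(Z > 1.645 − shift × √(38 − k)).

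- k = 2, ρ = 0.3: 1.645 − 0.032 × 6 = 1.453, giving 7.3%.
- k = 4, ρ = 0.5: 1.645 − 0.098 × 5.83 = 1.07, giving 14%.

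Both agree with the table. The remaining gap arises because trimming one tail also shrinks the SD.

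**Early versus delayed:** 19 v 19, two-sided t-test at 5% as a stand-in for the planned non-directional test.

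| Exclusions | ρ = 0.3 | ρ = 0.5 |
|---|---|---|
| 2, in one arm only | 5.4% | 6.1% |
| 4, in one arm only | 6.1% | 8.2% |
| 2 in each arm, same process | 5.2% | 5.5% |

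These are rates for a single test, before the false discovery rate correction planned for the five cytokines.

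**The case against.** **The SAP may define this.** A cut-off for adherence and the analysis sets are commonly left to a SAP, which is not shown. That stands against complaining of a missing threshold alone. It does not rescue the sentence: the article states a discretionary exclusion, and a SAP would have to override it.

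**Exclusion by arm.** A reader might infer that the early arm loses more patients because its staff must learn a new procedure. The text does not support this. The stress named comes from using the monitor, and Table 1 shows HR recorded in both groups in all six weeks. Both groups also change procedure, in week 3 or week 5. Differential exclusion is possible, but the documents do not establish it.

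**A larger effect.** A reader might take the worst case as the size of the problem: dropping the 1, 2 or 3 least favourable of 19 in one arm gives a one-sided error of about 10%, 16% and 22%. That needs perfect correlation with outcome, losses in one arm only, and a one-sided group comparison. The planned group comparison is not directional.

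**Whole patients.** The text speaks of data, so it may mean only unreliable registrations. The loss of blood and ECG results is therefore conditional.

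**Disclosure.** Removals will be reported, and HR increases without a registration are a planned count, so unworkable cases do not vanish from view. This stands as transparency. It does not correct a biased estimate.

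**Blinding.** The Discussion says "In this randomized blinded controlled trial, we aim to study HR to improve communication between patient and caregiver", which a reader might take to cover the exclusion decision. The Blinding section limits masking to the secondary-outcome analysis. Equally, calling the whole trial unblinded would ignore that masking. The label is a separate point.

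**Conclusion.** The point holds in moderate form. The article fixes a subjective exclusion, made after randomisation, without linking it to its own adherence data or masking it to HR data and allocation.

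The exposure lies mainly in the one-sided before-after tests. With a correlation of 0.3 to 0.5 and no true effect, the type I error is about 7% to 10% with 2 exclusions and 10% to 15% with 4. If exclusions filled the whole 15% dropout allowance (6 patients), it would be 12% to 21%. The group comparison for secondary hypothesis 1 is affected little unless exclusions cluster in one arm. The primary analysis compares situations within patients, so arm imbalance is not its issue, although exclusion related to its paired differences would bias it too.

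All sizes rest on an assumed number of exclusions, an assumed correlation and an assumed direction. With zero correlation there is no inflation. If the excluded cases had the more favourable changes, the rule would hide an effect instead. Nothing in the rule as stated secures the harmless case.

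**What to change.** Replace the exclusion sentence with three statements:

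1. All randomised patients with available data are analysed in their allocated group.
2. Blood and ECG outcomes are kept whatever the view of caregiver adherence.
3. Doubted adherence enters only a sensitivity analysis. It is defined by the responsiveness measure under Measures of treatment compliance (contexts recorded relative to HR increases), at a cut-off fixed before data are seen and applied masked to allocation and outcome. State whether that analysis drops registrations or patients.

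Keep the commitment to report the number and reason for removals, and give them by group. Decisions on whether a patient goes on wearing the monitor are untouched: this concerns only which collected data are analysed.

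The cost is a change of wording and one extra analysis. The downside is slight dilution of the main result by poorly adherent cases. The description of the trial as blinded in the Discussion should be handled separately and is not part of this change.
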